**Methods:**

This will be a pilot randomised controlled trial (RCT) comparing a strength-based digital smartphone application (Peer Tree) with a control condition. Forty-two young people enrolled at university will be recruited for this pilot RCT. Participants with suicidal ideation or behaviours, acute psychiatric symptoms in the past month, or a current diagnosis of a mood or social anxiety disorder will be excluded. Allocation will be made on a 1:1 ratio and will occur after the initial baseline assessment. Assessments are completed at baseline, at post-intervention, and at follow-up. Participants in the control condition complete the same three assessment sessions. The primary outcome of the study will be loneliness. Depression, social anxiety, quality of life, acceptability, usability, feasibility, and safety of Peer Tree will also be measured as secondary outcomes.

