##### Chat forum

Users of Peer Tree also have access to a moderated chat forum where they can discuss each module with their peers. A one-on-one chat function is also available for participants to contact other participants or moderators privately. There are four types of moderation in the peer tree study, all of which are in place to ensure participant safety. These include clinical, peer, research, and technical moderation.

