### Participant timeline {13}

The participant timeline is as follows:Screening: a brief phone call or face-to-face assessment to verify initial inclusion and exclusion criteria.The baseline assessment and secondary verification procedure will be conducted 1–7 days after screening.If eligible, participants will be randomised to either Peer Tree or control.Peer Tree participants will wait until a suitable number of participants is available to be onboarded onto the Peer Tree application. This will be dictated by recruitment speed. Once enough participants have been randomised to Peer Tree, the intervention will begin. After 6–8 weeks, participants will be seen for the post-intervention assessment.Control participants will wait for 6 weeks before starting the post-intervention assessment.Three months following the completion of the post-intervention assessment, participants will complete the third and final assessment. Once the follow-up assessment is complete, the study is completed.

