### Sample size {14}

A power analysis was conducted using G*Power 2.0 software. The *F* statistic function for an intervention design was used to obtain the relevant sample size. This is established using loneliness outcome data and is estimated using the effects sizes derived from +Connect. Loneliness was used to determine statistical power as it was the target variable of our primary outcomes. This revealed that 42 participants are needed to detect a moderate effect with 80% power.

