## Statistical methods

### Statistical methods for primary and secondary outcomes {20a}

All data processing and analysis will occur either in the statistical package for the Social Sciences (SPSS) or Mplus. Data manipulation will only occur if the data violates the statistical assumptions for the tests that we would be conducting. In this instance, the data will be transformed into a format that does not jeopardise the interpretability of the scores.

An intention-to-treat (ITT) analysis will also be conducted on all participants who were enrolled in the project but dropped out of the study. A mixed-model analysis will be used to determine whether a greater change in loneliness occurs over time for the Peer Tree group compared with the control group. This form of analysis creates an unbiased view of the intervention by including every participant who was assigned to each group in the final analysis, rather than those who contributed to each data point in the study. That is, if 15 people were assigned to an intervention but only nine of them completed the intervention, the ITT analysis would include all 15 participants in the analysis to provide an appropriate measure of what the effect would look like with every participant included.

A per-protocol analysis using mixed-model analysis of variance will be conducted to determine whether a change in loneliness occurs over time more so for the Peer Tree group compared with the control condition. Time (i.e. baseline, post-intervention, follow-up) will be the repeated measure factor, while intervention (i.e. Peer Tree vs control) will be the between-participant factor. Two-tailed Pearson’s *r* correlations will be calculated to assess the relationships between our primary outcome, loneliness, and secondary outcomes. This will be used to determine the suitability of conducting additional, regression-based analyses. In the instances that there are violations to the assumptions of these tests, we envisage that any combination of the following will be used to answer our focal questions: standard and hierarchical regression, mediation and multiple mediation, latent trajectory modelling, *t*-tests, and mean comparisons.

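### Peer Tree participants start in groups and share a forum, but neither the stated loneliness ANOVA nor the 80% power figure allows for correlation within that arm

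*Protocol article*

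**What the plan says.** **Design.** The abstract states "Allocation will be made on a 1:1 ratio", so 42 people give about 21 per arm, randomised individually. Participant timeline {13} has those allocated to Peer Tree wait for a group to form: "Once enough participants have been randomised to Peer Tree, the intervention will begin". The size of that group is left to the pace of recruitment. The Chat forum section says "Users of Peer Tree also have access to a moderated chat forum where they can discuss each module with their peers", and adds private messaging with other participants or with moderators. The sections on clinical, peer and research moderation describe moderators who serve the whole forum. The control arm has no grouping, forum or moderators.

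**Analysis.** Statistical methods {20a} sets out the per-protocol mixed ANOVA of loneliness with three time points as the repeated factor, and "intervention (i.e. Peer Tree vs control) will be the between-participant factor". For the ITT analysis it says only that a mixed model will be used; no fixed or random effects are listed.

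**Sample size {14}.** The F "statistic function for an intervention design was used to obtain the relevant sample size", with the effect "estimated using the effects sizes derived from +Connect". The result is given as "This revealed that 42 participants are needed to detect a moderate effect with 80% power". No numerical effect size, alpha, within-person correlation or number of measurements is given, and clustering is not mentioned.

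**The concern.** This is a partially nested design: individuals are randomised, but after randomisation one arm is placed in interacting groups and the other is not. The outcome is loneliness, and the Background presents bonds with peers as the main protection against it. A lively or a quiet batch could therefore shift its members together. That shared shift would enter the Peer Tree mean. A model with only time and arm would not count it as an extra source of uncertainty, because it treats the 21 Peer Tree participants as 21 independent units.

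At stake are the width of the confidence interval for the loneliness difference, the risk of reading a chance batch effect as an effect of the app, and the meaning of the stated 80% power.

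**Working it through.** **1. The plan's own figure.** N = 42 cannot be uniquely reproduced, because the inputs are not stated. Taking alpha 0.05, it is reached by individual-level repeated-measures F tests such as:
- group-by-time interaction with f = 0.20, m = 3 measurements and correlation ρ = 0.5: λ = f²Nm/(1−ρ) = 0.04 × 42 × 3 / 0.5 = 10.08 on (2, 80) df, power 0.803;
- between-group factor with f = 0.40, m = 3 and ρ = 0.7: λ = f²Nm/(1+(m−1)ρ) = 0.16 × 42 × 3 / 2.4 = 8.4 on (1, 40) df, power 0.807.

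Neither formula contains a clustering term.

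**2. Standard-error inflation.** Inputs: 21 per arm (from the document); ICC and batch sizes (assumed). With clustering in the Peer Tree arm only:
- arm design effect DE = 1 + (b − 1) × ICC, where b is the batch size (for unequal batches, Σb²/Σb);
- ratio of true to naive standard error = √((1 + DE)/2);
- power = Φ(2.8016/ratio − 1.96), which is 80% at ratio 1;
- N to keep 80% power ≈ 42 × (1 + DE)/2.

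At ICC 0.05:

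| Batches | b | DE | SE ratio | Power | N for 80% |
|---|---|---|---|---|---|
| seven of 3 | 3 | 1.10 | 1.025 | 78% | 44 |
| three of 7 | 7 | 1.30 | 1.072 | 74% | 48 |
| 11 + 10 | 221/21 = 10.52 | 1.476 | 1.113 | 71% | 52 |
| one of 21 | 21 | 2.00 | 1.225 | 63% | 63 |

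The last row is formal only: with a single group, the batch effect and the treatment effect cannot be separated.

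Power over other assumed ICCs:

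| Batches | ICC 0.01 | ICC 0.10 | ICC 0.20 |
|---|---|---|---|
| seven of 3 | 80% | 76% | 73% |
| three of 7 | 79% | 69% | 60% |
| 11 + 10 | 78% | 64% | 52% |
| one of 21 (formal) | 76% | 51% | 37% |

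**3. False-positive rate.** This was simulated at nominal 5% with 21 per arm, 20,000 to 60,000 trials per cell. The group-by-time F(2, 80) test used three occasions with correlation 0.5 and a batch effect in the Peer Tree arm after baseline only. A two-sample t test on a single contrast was run as a check. Ranges are over repeated runs.

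| Batches | F test, ICC 0.05 | t test, ICC 0.05 | F test, ICC 0.10 |
|---|---|---|---|
| seven of 3 | 5.3-5.9% | 5.7% | 5.8-6.1% |
| three of 7 | 6.5-6.8% | 6.9% | 8.3-9.0% |
| two | 7.5-8.1% | 7.7% | 10.4-10.9% |
| one of 21 | 10.8-11.2% | 11.0% | 17.2-17.9% |

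At ICC 0 every pattern returns about 5%. At ICC 0.01 the t test runs from 5.0% (seven of 3) to 6.2% (one of 21).

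**The case against.** **The size rests on assumptions.** A reader might infer that the false-positive rate does exceed 5%. The article does not support that: it gives no ICC, batch size or number of batches. With small batches and a small ICC the excess is negligible, and the 11-18% figures come only from treating all 21 as one group. If the whole package, peer contact included, affects nobody, individual randomisation keeps the test at 5%. The excess arises where batches move people up or down with no average effect. This objection stands, so the point must be conditional.

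**The quoted factor belongs to the per-protocol analysis.** A reader might infer that the ITT model also leaves out batch. The article does not say so. It leaves the random effects open, and an analysis plan that is not shown may settle them. This also stands.

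**Batch may not be the right unit.** The article does not say that each batch has its own forum. One forum may serve all users, or there may be a single start. In either case a batch effect would not capture all the clustering, or could not be estimated at all. This stands and shapes the fix.

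**Power could look much worse.** A test on batch means at ICC 0.05 has about 74%, 59% and 51% power with seven, three and two batches, and a reader might take the whole shortfall as the cost of clustering. Most of it is not: at ICC 0 the same test already has only about 76%, 68% and 61%, because it has few degrees of freedom. The standard-error figures in the working are the fair ones.

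**What survives.** The factors that {20a} does state, and the power that {14} states, do not fit the grouped delivery described in {13} and the Chat forum section.

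**Conclusion.** The point holds in conditional form. The Peer Tree arm is grouped by design, while the stated ANOVA and the power statement treat its members as independent. If the within-batch ICC is above 0, the standard error is understated. At an assumed ICC of 0.05, the false-positive rate at nominal 5% is about 5.5% (seven batches of 3), 6.5-7% (three of 7), 8% (two) or 11% (one group). Power is about 78%, 74%, 71% or 63% in place of 80%, the last being formal only.

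These figures rest on the assumed ICC, the assumed batch patterns, 21 per arm with no dropout and, for the F test, a within-person correlation of 0.5. The effect is small with many small batches and material with one or two. For the ITT model the finding is only that the article does not describe how clustering is handled.

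**What to change.** - **Data.** Record each Peer Tree participant's onboarding batch and forum membership.
- **Statistical methods {20a}.** Keep the individual-level model as the main analysis. Add a pre-specified sensitivity analysis with a random batch effect in the Peer Tree arm only, after baseline, with controls as singletons and Satterthwaite or Kenward-Roger degrees of freedom. Report the ICC with its interval beside the group difference.
- **If there is only one batch or one common forum.** State that the group effect cannot be separated from the effect of the app, and that the p-value assumes no clustering.
- **Sample size {14}.** State that 80% power assumes independent participants, and show the figure over a range of assumed ICCs and batch counts, as in the working.

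**Cost.** One variable that onboarding already produces, and some wording; no extra participants. The stated power becomes less favourable. With two to four batches the ICC is poorly estimated and the sensitivity analysis has low power. In simulation at ICC 0.05, the batch-means test had a false-positive rate of 5.2-5.8% with three or more batches, but 7.9% with two, hardly better than the unadjusted F test. It should therefore support the main model and not replace it.

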## Objectives {7}

The objective of this study is to evaluate the acceptability, feasibility, safety, and initial efficacy of a positive psychology smartphone application intervention called Peer Tree. Peer Tree is a digital smartphone intervention targeting loneliness and is a new iteration of our previous application +Connect. Peer Tree includes many features from +Connect [30, 31] but also includes the personalisation of modules based on user symptom profiles, a peer- and clinician-moderated chat forum, and animated videos to address loneliness in young people using a positive psychology framework.

It is hypothesised that Peer Tree participants, compared with the control participants, will report significantly lower loneliness at post-intervention, and these effects will remain at follow-up. It is also anticipated that Peer Tree participants, compared with control participants, will report significantly lower social anxiety and depressive symptoms, and higher quality of life and well-being outcomes at post-intervention as well as at follow-up.

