### Outcomes {12}

See Table 1 for the SPIRIT schedule of measures used in this study. The primary outcomes are loneliness, acceptability, feasibility, and safety of Peer Tree. Secondary outcomes include social anxiety, depression, quality of life, and psychological well-being. Demographic variables will include age, gender, sexuality, ethnicity, work status, level of education, previously attempted university degrees, current university course load, postcode, and religion.

**Table 1 Tab1:** SPIRIT schedule of outcome measures

Outcome measures	Baseline	End of treatment	Follow-up
Enrolment			
Eligibility screen	X		
Informed consent	X		
Allocation	X		
Assessments			
Demographic form	X		
UCLA-LS3	X	X	X
SIAS	X	X	X
CES-D	X	X	X
LSNS-18	X	X	X
IIP-32	X	X	X
PWB-54	X	X	X
PANAS-SF	X	X	X
WHO QOL-Bréf	X		
COVID-19 question	X	X	X
Adherence		X	
Mean Peer Tree application acceptability		X	
Mean Peer Tree application feasibility		X	
Mean Peer Tree application usability		X	

*UCLA-LS3* UCLA Loneliness Scale-Version 3, *SIAS* Social Interaction Anxiety Index, *CES-D* Centre for Epidemiological Studies-Depression, *LSNS* Lubben Social Network Scale, *IIP-32*, Inventory of Interpersonal Problems, *PWB* Scales of Psychological Wellbeing, *PANAS-SF* Positive and Negative Affect Scale–Short Form, *WHO QOL-Bréf* World Health Organization Quality of Life-Bréf

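### No committed analysis compares the arms on the secondary outcomes: both arm-by-time models are for loneliness, and the correlation named for secondary outcomes has no arm term

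*Protocol article*

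**What the plan says.** Protocol article, Objectives {7}: Peer Tree participants, set against controls, "will report significantly lower social anxiety and depressive symptoms, and higher quality of life and well-being outcomes at post-intervention", and the same is expected at follow-up. These are between-arm statements.

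Outcomes {12}: "Secondary outcomes include social anxiety, depression, quality of life, and psychological well-being". Table 1 in that section schedules the social anxiety (SIAS), depression (CES-D) and well-being (PWB-54) scales at baseline, end of treatment and follow-up. WHO QOL-Bréf is marked at baseline only.

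Statistical methods for primary and secondary outcomes {20a}:

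- Intention to treat: "A mixed-model analysis will be used to determine whether a greater change in loneliness occurs over time for the Peer Tree group".
- Per protocol: a mixed-model analysis of variance "will be conducted to determine whether a change in loneliness occurs over time more so for the Peer Tree group", with three levels of time and arm as the between-participant factor.
- Secondary outcomes: two-tailed Pearson "correlations will be calculated to assess the relationships between our primary outcome, loneliness, and secondary outcomes", followed by "This will be used to determine the suitability of conducting additional, regression-based analyses".
- Fallback: an open list, including regression, mediation, t-tests and mean comparisons, for use where the assumptions of the tests are violated.

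**The concern.** The section heading promises methods for the secondary outcomes, and the only sentence in it that names them gives an analysis for a different question. A correlation between loneliness and, say, depression asks whether two scales move together across students. The hypotheses ask whether the arms differ. Background and rationale {6a} already reports that loneliness predicts anxiety, stress and depression in university students, so such correlations are to be expected with or without an effective app.

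At stake is whether the secondary hypotheses are tested by a rule fixed in advance. As the text stands, an analyst who follows it literally has no arm comparison to run on any secondary outcome. One who adds such comparisons after seeing the data is choosing the method post hoc.

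**Working it through.** **1. Each hypothesis beside its analysis.**

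| Outcome (Objectives {7}) | Scale | Scheduled after baseline (Table 1) | Committed arm comparison ({20a}) |
|---|---|---|---|
| Loneliness | UCLA-LS3 | yes, both visits | yes, two mixed models |
| Social anxiety | SIAS | yes, both visits | none |
| Depression | CES-D | yes, both visits | none |
| Well-being | PWB-54 | yes, both visits | none |
| Quality of life | WHO QOL-Bréf | no | none |

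Four secondary outcomes at two visits make 4 × 2 = 8 hypothesised arm contrasts. The text commits to 0 of the 8. With the present schedule, 3 × 2 = 6 could be estimated. The 2 for quality of life could not.

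**2. What the correlation tests.** Its data are the pairs (loneliness, secondary scale), and its null is that their correlation ρ is zero. The hypotheses have the null that the secondary scale's mean is equal in the two arms. Either null can hold while the other fails:

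- *No arm effect, scales related.* The arm null is true and the correlation null is false.
- *Arm effect on the secondary scale only, scales unrelated within arms.* The arm null is false, yet the pooled correlation is still zero because loneliness does not differ by arm.

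An arm effect on both scales does feed into a correlation pooled over arms, but only weakly. With unit within-arm variances, zero within-arm correlation, equal arms and a shift of 0.8 SD in the same direction on both scales, the covariance is 0.8 × 0.8 / 4 = 0.16. Each variance is 1 + 0.16 = 1.16, so the pooled correlation is 0.16 / 1.16 = 0.14. A correlation of that size can equally arise with no arm effect, so the statistic cannot tell the two apart.

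**3. Illustration only.** The documents give no correlation, no alpha and no cut-off for suitability. All three are assumed here: ρ as shown, p < 0.05 two-sided, bivariate normal data, 42 participants in two arms of 21, 40,000 simulated trials per case.

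| Case | Pearson p < 0.05 | Arm t-test on secondary scale p < 0.05 |
|---|---|---|
| No arm effect, ρ = 0.3 | 50% | 5% |
| No arm effect, ρ = 0.5 | 94% | 5% |
| 0.8 SD arm effect on secondary scale only, ρ = 0 | 5% | 72% |

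The first two Pearson entries are the power of a correlation test at the assumed ρ. They show that a correlation can be significant with no treatment effect. They are not false-positive rates of this plan.

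**4. The fallback list.** T-tests and mean comparisons appear there, but they apply only if assumptions fail, are offered in any combination, and are not tied to a secondary outcome. If assumptions hold, they are not called on.

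**The case against.** The strongest reply is that the correlation was never offered as the test of the secondary hypotheses. Its stated purpose is to describe relationships and then to judge whether additional regression work is suitable, and looking at associations before such work is ordinary practice. That is right. A reader might infer that the correlation is a gate through which every secondary outcome must pass before the arms are compared. The text does not say so: it ties the correlation to additional regression-based analyses only. Nor does it say that a significant correlation would count as evidence for the app, or that suitability means p < 0.05. The percentages above therefore do not measure a harm in this trial.

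The second reply is that extending the primary model to the other scales is detail that an article leaves to the analysis plan. The section heading covers secondary outcomes and most scales share the three visits, so the same model may be intended. Had the section been silent, this would settle the matter. It is not silent: it limits both models to loneliness and then gives the secondary outcomes a different method, one that does not match the hypotheses. What stands of this reply is that the omission may be one of drafting and that a full analysis plan may already contain the comparison.

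**Conclusion.** The point holds as a mismatch between objective and method. Four between-arm secondary hypotheses are stated, and none has a committed analysis. The one analysis named for secondary outcomes cannot supply one, because arm does not enter it. This follows from the wording alone and needs no assumed correlation or alpha. It rests on the article as printed, since no separate analysis plan was available.

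The size is moderate. The loneliness analysis is untouched, the data for three of the four outcomes will exist at both later visits, and the gap closes with a short addition. Quality of life is the exception: no change of analysis can test that hypothesis while its scale is scheduled at baseline only.

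**What to change.** In Statistical methods {20a}, state that:

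1. The intention-to-treat mixed model used for loneliness (arm, time, arm-by-time) will be fitted to each secondary scale measured after baseline.
2. Baseline is handled in one way only: either as a level of the time factor, or as a covariate with post-baseline responses. It should not be both response and covariate.
3. The arm difference at post-intervention and at follow-up is reported with a 95% confidence interval and labelled supportive.
4. The correlations with loneliness are descriptive, and no secondary arm comparison depends on them.

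Separately, reconcile Table 1 with Objectives {7} on quality of life. Either the schedule is an error to be corrected, or the post-baseline quality-of-life hypothesis cannot stand.

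The cost is a few sentences and some extra model fits on data the trial already collects, apart from any change to the WHO QOL-Bréf schedule. The downside is several supportive tests without multiplicity control. For the three hypothesised outcomes with post-baseline data there are 6 contrasts, so at an assumed alpha of 0.05 about 6 × 0.05 = 0.3 would be significant by chance if nothing differed. That is why they should be labelled supportive.

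### The plan does not say which loneliness analysis leads, and if assumptions fail it allows an unordered choice among other methods; the list of primary outcomes also differs between sections

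*Protocol article*

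**What the plan says.** Statistical methods {20a} gives loneliness two main analyses: an intention-to-treat mixed model, and a per-protocol mixed-model analysis of variance with time (three visits) and group as factors. Neither is called primary.

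The same section has two responses to violated assumptions. The first is transformation: "Data manipulation will only occur if the data violates the statistical assumptions for the tests that we would be conducting", in which case "the data will be transformed into a format that does not jeopardise the interpretability of the scores". The second is a change of method. Here the protocol says "we envisage that any combination of the following will be used to answer our focal questions", and the only condition it sets on this is "In the instances that there are violations to the assumptions of these tests". The list it gives is "standard and hierarchical regression, mediation and multiple mediation, latent trajectory modelling", then t-tests and comparisons of means. That is five list items, or seven methods if the paired items are split. Pearson correlations between loneliness and the secondary outcomes are also planned, and of these the section says "This will be used to determine the suitability of conducting additional, regression-based analyses".

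On the primary outcome, the Abstract (Methods) says "The primary outcome of the study will be loneliness" and makes acceptability, feasibility and safety secondary. Statistical methods {20a} also treats loneliness as the single primary outcome. Outcomes {12} says "The primary outcomes are loneliness, acceptability, feasibility, and safety of Peer Tree", yet the descriptions of acceptability, feasibility and safety stand under its Secondary outcomes heading.

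**The concern.** A fallback rule limits the analyst only if it says what sets it off and what then replaces the main model. This one does neither. It names no diagnostic and no threshold, does not say whether transformation or a change of method comes first, and lets methods be combined freely. It is directed at the focal questions, so it can reach the loneliness hypothesis itself.

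Many of the listed methods are not remedies. If residuals are skewed or variances unequal, standard t-tests and linear regression rest on the same assumptions as the model they replace. Mediation estimates a pathway, not the between-arm difference.

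The setting makes this matter more. Under Who will be blinded {17a} no researcher is blinded, and Trial status says data collection had begun. The Objectives predict significantly lower loneliness, and the sample size is justified by 80% power for it. A reported significant result would be read as the planned efficacy finding, although the analysis behind it could have been picked from several.

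**Working it through.** **Inputs.** 42 participants and 1:1 allocation (Abstract), so 42/2 = 21 per arm. Three visits (Statistical methods {20a}). The protocol states no significance level and no between-visit correlation; two-sided 5% and a correlation of 0.6 are assumptions, with normal data, equal correlation between visits and no true effect. The plan gives no error rate of its own to reproduce.

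**Step 1: bound.** For k independent tests at 5%, the chance of at least one false positive is 1 − 0.95^k. For k = 3 this is 1 − 0.857 = 14.3%; for k = 6 it is 1 − 0.735 = 26.5%. Tests on the same participants are correlated, so the true figures are lower and need simulation.

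**Step 2: free choice, fallback always used.** Each of 20,000 null trials was analysed by a t-test on scores, a t-test on change from baseline and a baseline-adjusted regression. A false positive is any p < 0.05.

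| Analyses open to choice | False-positive rate |
|---|---|
| One fixed test | about 5% |
| Best of three at post-intervention | about 10% |
| Best of six (three at each of two visits) | about 17% |

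With correlations from 0.3 to 0.7 the last two rows run from 9.1% to 10.0% and from 16.7% to 17.5%. A different set of six tests (mixed analysis of variance; t-test and adjusted regression at each visit; slope) gives 16.2% to 16.7% at correlations of 0.5 and 0.7. Mediation models and transformed scores were not simulated.

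**Step 3: fallback used only after a trigger.** Suppose switching requires a Shapiro-Wilk rejection at any visit. This trigger is an assumption, since the protocol gives none. With normal data it is met in about 14% of trials, and the simulated rates are about 5.8% (best of three) and 6.8% (best of six). If q is the proportion of trials that switch, and switching is roughly unrelated to the test result, the rate is about (1 − q) × 5% + q × (free-choice rate):

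- q = 0.14: 0.86 × 5% + 0.14 × 10% = 5.7%; 0.86 × 5% + 0.14 × 17% = 6.7%.
- q = 0.50: 0.50 × 5% + 0.50 × 10% = 7.5%; 0.50 × 5% + 0.50 × 17% = 11.0%.
- q = 1: 10% and 17%, as in step 2.

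The excess therefore depends on how often the fallback is invoked, which the protocol leaves undefined.

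**Step 4: choice of population, no violation needed.** Taking whichever of the intention-to-treat and per-protocol mixed models is significant gives 6.8% to 7.1% (correlations 0.7 and 0.5). This assumes about 30% of the app arm is excluded at random (15 of 21 kept). Real per-protocol exclusions are unlikely to be random and could add bias as well.

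**Step 5: one or four primary outcomes.** Acceptability is a set of ratings of the app, feasibility is judged against thresholds, and safety is a rule on reported events. None has a between-arm test, so calling them primary adds no false-positive risk.

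**The case against.** The strongest defence is that the plan does name a main model, with its factors, and allows alternatives only after a violation. The clause on violated assumptions also follows directly on the correlations and regressions, so it may not cover the mixed model at all. The trial is a pilot of initial efficacy, and a separate analysis plan may hold the detail. Some listed methods do help with one violation: t-tests, single-visit regression and trajectory models do not need the sphericity assumption of a three-visit analysis of variance. The hypothesis also asks for an effect at post-intervention that persists; requiring significance at both visits under the same free choice gives only about 2.5%.

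Much of this stands. A reader might infer that there is no planned test, or that the error rate is 17%. The documents support neither: a model is named, and 17% needs the fallback in every trial and success at either visit. A reader might also infer that four primary outcomes inflate the error rate, or that a stated 5% level is breached. Three of the four carry no test, and no level is stated.

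What the defence does not answer is that a condition with no criterion constrains little, that the clause refers to the focal questions, and that the choice between intention-to-treat and per-protocol is open without any violation. Nor is this simply detail left to another document: the protocol states the rule, and the rule permits any combination. Whether the three-visit interaction or a single-visit contrast is better is partly preference, but which of them carries the claim should be fixed.

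**Conclusion.** The concern holds in limited form. The main model is named, but its analysis population is not fixed and its fallback is open-ended, so the headline loneliness result can be selected after the data are seen. At an assumed two-sided 5%, the cost runs from about 6% to 7% when a formal normality check gates the switch and the data are normal, up to about 10% (post-intervention only) or 17% (either visit) if the fallback is always used. Clearly non-normal data would trigger the switch more often and move the rate towards the upper figures. All of these show what the rule permits under the stated assumptions; they do not forecast what the investigators will do.

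The disagreement between the Abstract and Statistical methods {20a} on one side and Outcomes {12} on the other is real. It is a separate matter of labelling, with no effect on type I error.

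**What to change.** Before analysis:

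- In the Abstract, Outcomes {12} and Statistical methods {20a}, name UCLA-LS3 at post-intervention as the single primary efficacy endpoint. Make follow-up secondary, and acceptability, feasibility and safety descriptive. Sample size {14}, which speaks of primary outcomes in the plural, should match.
- Make the primary analysis the between-arm contrast at post-intervention in all randomised participants (intention-to-treat), from a mixed model with baseline UCLA-LS3 as covariate, at a stated two-sided alpha. Per-protocol becomes a sensitivity analysis.
- State which residual checks will be made. If they fail, keep the same contrast on the original scale and report robust or bootstrap intervals. This replaces both transformation and change of method for the primary analysis.
- Delete the any-combination sentence for the focal question, and label correlations, regression, mediation and trajectory models exploratory.

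The cost is a few sentences. Analysts lose the freedom to choose the model for the headline result; the other analyses can still be run and reported as exploratory.
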